##### Home-based program

A booklet of exercises is given to each participant at the end of the first session of the training program. The exercises in this home-based program are taught during the supervised training program sessions. The participants are instructed to perform the exercises on a daily basis for approximately ten minutes, at home, once the training program is finished.

#### Control group: usual treatment program

Control group members do not benefit from specific treatment of low back pain aside from any treatment undertaken on their own initiative (such as physiotherapy or mesotherapy). Information regarding the treatment program followed by each participant is collected by the occupational health physicians at the inclusion visit and during the follow-up visits.

### Implementation of the study

#### Baseline assessment

Baseline data (administrative, socio-demographic and socio-professional data, as well as information regarding the history of their condition) are collected by the occupational health physicians.

After his inclusion in the study, each participant, regardless of group, underwent an individual assessment with a physiotherapist from Centre Médico-Chirurgical et de Réadaptation des Massues – Croix Rouge Française, as well as an X-ray assessment of the spinal column. The clinical characteristics of the participants in terms of deficiencies, disability and handicap were collected during the initial assessment with the physiotherapist using clinical examination and self-administered questionnaires. The lumbopelvic morphotype of each participant was determined using the X-ray assessment of the entire spinal column carried out in the Radiology Department of the Hôpital Femme-Mère-Enfant (Groupement Hospitalier Est, Hospices Civils de Lyon).

#### Follow-up visits

All of the participants were followed for two years: either for the two years following the beginning of the global program for those in the intervention group, or for the two years following randomization for those in the control group. This monitoring was provided by the occupational health physician in the participant’s workplace (one appointment after 12 months and the other after 24 months) and by a physiotherapist from the Centre Médico-Chirurgical et de Réadaptation des Massues – Croix Rouge Française (one appointment after 18 months).

During the 12-month follow-up visit, the intervention group members participating in the evaluation of the operational model of the PRESLO study underwent a semi-structured interview with a member of the research team, immediately following the evaluation by the occupational health physician.

Participants’ presence at follow-up visits and sessions is continually verified using the attendance sheets transmitted by the physiotherapists. Participants who miss an assessment or an appointment are reminded by the Clinical Research Assistant from the data coordinating center concerning their participation in the study or questioned regarding their reasons for absence.

Outcomes

Primary outcome

Percentage of participants with at least one recurrence of low back pain in the two years following the end of the global program.

Secondary outcomes

1. Average time to recurrence of low back pain during the study period.

2. Percentage of participants with a sick leave related to a chronic low back pain (pain for more than three months) in the two years following the end of the global program.

3. Evaluation of the compliance of the participants in the global program.

4. Feedback from the participants in the global program.

5. Feedback from the health care professionals providing the program (physiotherapists and occupational health physicians).

A recurrence is defined as a new episode of low back pain leading to a sick leave. The occupational health physicians of each workplace have access to the date and duration of the work interruptions declared for each participant and can learn the motives from the participant at the annual checkups. The collection of information regarding low back pain recurrence will therefore be comprehensive.

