### Intervention

#### Intervention group: global prevention program

The global prevention program procedure is presented in Figure
2. This program requires approximately two months and is based on the management of low back pain on both the cognitive level (information about pain pathways and the factors favoring the development of chronification) and the physical level (implementation of an education and training program followed by a home-based program).

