### Analysis of the primary outcome

The percentage of patients with at least one recurrent episode of low back pain during the 2-year follow-up will be compared between the 2 study groups using a chi-squared test. The prognostic factors and the possible interactions between covariables will be tested with the use of Mantel-Haenszel chi-squared analysis. A multivariate logistic regression analysis will be performed to evaluate the effectiveness of the global program after controlling for potential confounding variables.

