
From a methodological viewpoint, however, the absence of a double-blind design and of a placebo control group could introduce bias into the interpretation of the results. That said, the very nature of the evaluated intervention did not allow such a design. Cluster randomized trials, with departments randomized instead of individuals, could also have been chosen in order to alleviate non-blinded bias and the non-negligible risk of contamination between the two study groups. This possibility could nevertheless not be retained due to the diverse nature of the participants’ departments of origin. The proposed study is therefore an open randomized trial. The primary outcome, which is low back pain recurrence as quantified by related work absence is, however, an objective criterion. Also, participants in the intervention group were requested not to discuss the global secondary prevention program with the other participants. As for the potential loss of opportunity for the participants randomized into the control group, it was partially resolved through offering these participants the chance to take part in the information session of the global program following their 24-month monitoring period.

It is possible that some participants may concurrently take part in the training sessions dealing with the handling of patients or loads that the Hospices Civils de Lyon offer to all personnel whether or not they suffer from low back pain. These sessions are more general than the global program and should instead be considered as a primary prevention strategy. They are therefore not specifically oriented toward the treatment of low back pain and its recurrences. Their efficiency in terms of secondary prevention has never been demonstrated. Information regarding the participants’ possible involvement in these training sessions will be collected and taken into account in the analysis of data. In particular, the comparability of this criterion will be verified for the two groups.

Inclusions for this study began in October 2008. The results concerning the program’s impact on low back pain recurrence risk will be known during the first semester of 2014, since the follow-up of the last participants included is to reach conclusion at the end of 2013.

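### Follow-up and outcome windows use three different time origins, so the arms are observed over different intervals since randomization and a difference can arise without any program effect

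*Protocol article*

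**What the plan says.** Under Follow-up visits, the Protocol article runs the observation period for "the two years following the beginning of the global program for those in the intervention group, or for the two years following randomization" in the control group. The same section places occupational-physician visits at 12 and 24 months.

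The outcome list further down moves the origin. The primary outcome is the "Percentage of participants with at least one recurrence of low back pain in the two years following the end of the global program". The chronic-pain outcome is the "Percentage of participants with a sick leave related to a chronic low back pain (pain for more than three months) in the two years following", again counted from program end. The first secondary outcome is the "Average time to recurrence of low back pain during the study period", with no origin given.

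Analysis of the primary outcome compares participants "with at least one recurrent episode of low back pain during the 2-year follow-up" by a chi-squared test and does not say when the two years begin. On the length of the program, the intervention section says: "This program requires approximately two months".

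**The concern.** Randomization makes the arms comparable from the moment of allocation. That protection carries over to the outcome only if both arms are observed over the same interval from allocation. Here the control clock starts at randomization. The intervention clock starts either when the program begins or when it ends, depending on which sentence the analyst follows.

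There are three consequences:

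- A sick leave for back pain after randomization but before the intervention window opens is an event for a control and a non-event for an intervention participant.
- Read literally, the primary and chronic-pain outcomes have no window for controls, who have no program end.
- If the 24-month visit is timed from program start, it falls about two months before two years after program end is complete. Physicians learn the reason for a sick leave from the participant at checkups, so the last stretch of that window has no scheduled visit.

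The Kaplan-Meier, logrank and Cox analyses also need one time zero, and none is given. At stake is the type I error of the primary comparison.

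**Working it through.** **Inputs from the Protocol article.** Recurrence rate 45%, relative reduction 25%, 310 per group, 80% power and 5% type I error (Number of subjects required); two-sided tests (Analysis); program of about two months (Intervention group).

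**Assumptions.** The 45% is taken as the control risk at 24 months; the article attaches no period to it. The wait between randomization and program start is not given, nor is the shape of the hazard over time.

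**The plan's own figure.** The target is 45% against 0.75 × 45% = 33.75%, a difference of 11.25 points. The two-proportion formula gives 295 per group without continuity correction and 313 with it, so 310 is reproduced to within 3%. The sample size is not in question.

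**Model with no program effect.** The cumulative hazard is H(t) = −ln(0.55) × (t/24)^k = 0.5978 × (t/24)^k. The risk over a window from month a to month b is 1 − exp{−[H(b) − H(a)]}. Controls are counted over months 0–24, which gives 45.0% for every k. A two-month shift arises if the program starts two months after randomization and the window opens at its start, or if it starts at once and the window opens at its end.

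**Rejection probability.** This is for the two-sided 5% pooled two-proportion test with 310 per arm.

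Worked case, constant hazard (k = 1), intervention counted over 22 months:
- Hazard per month: 0.5978/24 = 0.02491.
- Risk: 1 − exp(−22 × 0.02491) = 42.2%, a difference of 2.8 points.
- Pooled standard error: √(2 × 0.436 × 0.564/310) = 0.0398, so the critical difference is 1.96 × 0.0398 = 0.0781.
- Rejection: P[Z > (0.0781 − 0.0281)/0.0398] + P[Z < (−0.0781 − 0.0281)/0.0398] = 0.105 + 0.004 = 10.9%.

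| Hazard | Intervention window (months since randomization) | Intervention risk | Control minus intervention | Rejection |
|---|---|---|---|---|
| Constant (k = 1) | 2–26 | 45.0% | 0 | 5.0% |
| Constant (k = 1) | 2–24 (22 months) | 42.2% | +2.8 points | 10.9% |
| Falling (k = 0.8) | 2–26 | 42.6% | +2.4 points | 9.2% |
| Falling (k = 0.7) | 2–26 | 41.0% | +4.0 points | 17% |
| Rising (k = 1.3) | 2–26 | 47.3% | −2.3 points | 8.7% |

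For example, with k = 0.7, (26/24)^0.7 − (2/24)^0.7 = 1.0576 − 0.1756 = 0.882; 0.5978 × 0.882 = 0.527; 1 − exp(−0.527) = 41.0%.

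Against the planned 11.25 points, 2.8 points is 25% and 4.0 points is 36%.

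**With a common origin.** If both arms are counted over months 0–24 from randomization, the expected difference under no effect is 0 and the rejection probability is 5%, whatever the hazard shape or delay.

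**The case against.** The strongest reply is that the analysis section refers to the two-year follow-up, which the follow-up section defines for each arm. On that reading both windows last 24 months, controls do have a window, and the reference to the program's end is loose wording. The 22-month window is stated nowhere: it takes its opening from one sentence and its close from another. It could arise if the last visit caps the data, but physicians also have access to sick-leave dates. The exact index date for survival analyses is often left to an analysis plan, which is not shown here.

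This has force on length but not on origin. Two windows of 24 months that start at different times since randomization are still different windows, and the document itself sets the origin separately for each arm.

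Three stronger inferences are tempting, and the documents do not support them:

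- **That the bias must favour the program.** This needs a falling hazard or a shorter intervention window. Participants qualify through an episode at any time in the past three years, and a current acute episode excludes them, so randomization is not the onset of an episode and a steep early fall in risk cannot be presumed. If intervention events were counted from randomization to 24 months after program end, the bias would reverse. With a two-month wait and constant hazard, 28 months of exposure gives 50.2% against 45.0%.
- **That the dates show a five-month delay.** Inclusion ran to July 2011, and "the follow-up of the last participants included is to reach conclusion at the end of 2013". The second date is a rounded forecast for the last entrants. The 29 months may include scheduling slack, and they say nothing about the delay for everyone else.
- **That an intention-to-treat analysis cannot place non-starters.** The allocation letter gives intervention participants their session timetable, so a scheduled date exists. What is missing is a statement of which date applies.

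**Conclusion.** The contradiction stands on the text alone: there are three origins, one of which does not exist for controls, and no sentence reconciles them. The unequal origin remains even on the most favourable reading. A difference can therefore appear under no effect.

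Its size runs from zero to material, and it can go in either direction. The figures rest on an assumed 45% control risk at 24 months, an assumed two-month shift and assumed hazard shapes; they illustrate the exposure and do not estimate the bias in this trial. High confidence attaches to the contradiction and the unequal origin, not to any one figure. Because the primary comparison is affected and the result can depend on which sentence the analyst follows, the origin must be fixed before the data are analysed.

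**What to change.** Define the primary outcome in both arms as at least one sick leave for low back pain within 24 months of randomization, counted from the day of randomization whether or not the program was started or completed. Use the same origin and horizon for the chronic-pain outcome, and the same time zero for the Kaplan-Meier, logrank and Cox analyses. Align the follow-up, outcome and analysis sections to this wording.

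A window that opens at program end can stay as a secondary analysis if each control receives a matched index date.

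The cost is wording. Physicians already have access to the dates of work interruptions. The control visit falls at 24 months from randomization and the intervention visit at or after that point, so no visit needs to be added. The planned 310 per group is unchanged. The one downside is that recurrences before the program can act are counted, which slightly dilutes the effect.

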#### Other parameters

##### Evaluation of deficiencies

Information relative to impairments is collected by the physiotherapist at the baseline and the 18-month follow-up visits.

Nature of the evaluation of impairments

1. Pain assessed using the short-form Saint-Antoine pain questionnaire
[4] (QDSA)

2. Intensity of lumbar and radicular pains using a visual analog scale (in mm) between 0 (no pain) and 100 (pain of highest intensity)

3. Lumbar flexibility using the Schöber-MacRae test
[5]

4. Greater and lesser pelvic flexibility using finger-ground distance

5. Hamstring flexibility using the thigh-to-leg angle (with coxofemoral joint at 90°)

6. Rectus femoris flexibility using the heel-to-buttock distance in prone position

7. Abdominal endurance (Shirado test)
[6]

8. Lumbar extensor endurance (Sorensen test)
[7,8]

9. Gluteal endurance (gluteals test)

10. Quadriceps endurance (Killy test)

##### Assessment of functional disabilities

Functional disability is assessed with the French version of the Quebec Back Pain Disability Scale
[9,10], Its aim is to take into account the functional limitations linked to pain, in order to monitor the situation of low back pain sufferers enrolled in rehabilitation programs. An evaluation is planned at the baseline and the 18-month follow-up visits.

##### Assessment of lumbopelvic morphotype

An X-ray assessment of the entire spinal column is carried out at the start of the study for each participant by the Radiology Department of the Hôpital Femme-Mère-Enfant (Groupement Hospitalier Est, Hospices Civils de Lyon). This department is equipped with the EOS™ medical imaging system
[11]. This machinery offers features that justify its use in a study of this type, such as considerable reduction in X-ray dose (eight to ten times less for 2D radiology, 800 to 1000 times less for 3D radiology), examination of the patient in a standing position allowing simultaneous front and lateral X-ray views from the top of the head to the soles of the feet, and the option of reconstructing every level of the osteo-articular system in 3D.

Two simultaneous views (front and lateral) are obtained from the top of the head (entire spinal column) to the tibial plateaus. The X-ray assessments are then analyzed using OPTISPINE® software (SMAIO Company) in cooperation with Centre Médico-Chirurgical et de Réadaptation des Massues – Croix Rouge Française, in order to determine the sagittal balance of each participant.

##### Assessment of handicap and functional impact

The arduousness of working conditions as well as job satisfaction are evaluated at the baseline and the 18-month follow-up visits using a numerical scale from 0 (not at all satisfied) to 10 (completely satisfied).

Anxio-depressive disorders are quantified at the baseline and 18-month follow-up visits with the Hospital and Anxiety Depression (HAD) scale
[12].

The sensation of pain and the psychological experience of pain are evaluated at the baseline and the 18-month follow-up visit with the French version of the Fear Avoidance Beliefs Questionnaire (FABQ)
[13-15]. These scores evaluate the fears, beliefs and attitude of the low back pain sufferer with respect to physical activity.

The coping strategies employed by the participants to address their pain are assessed at the baseline and the 18-month follow-up visits with the French version of the Coping Strategies Questionnaire (CSQ-F) (Rosenstiel and Keefe, 1983)
[16,17]. Used in spinal pathology
[18,19], this questionnaire permits the assessment of the psychological adaptation strategies used by patients faced with a pain-inducing stressor.

##### Assessment of quality of life

The quality of life of the participants is evaluated by a physiotherapist at the baseline and the 18-month follow-up visit with the SF-12 self-administered questionnaire, which is a short version of the Medical Outcomes Study Short-Form General Health Survey (SF-36). It allows the measurement of eight aspects of quality of life: general and mental health, physical and social functioning, physical and “emotional” health, pain and vitality
[20].

##### Assessment of compliance with the global program

Compliance with the home-based program exercises is measured using two different approaches.

The first approach, quantitative evaluation, refers to the feedback gathered 6, 12 and 24 months after the end of the global program in terms of the number of different exercises performed, the number of weekly sessions and the weekly duration of exercises. A questionnaire is sent to the participants each time.

The second approach, qualitative evaluation, considers the quality of execution of the exercises. In this case, compliance is evaluated by the physiotherapist during the 18-month follow-up visit using a five-class semi-quantitative ordinal scale (null, poor, average, good and perfect).

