**Methods/Design:**

This study is a two-arm parallel randomized controlled trial proposed to all low back pain sufferers among HCL workers, included between October 2008 and July 2011 and followed over two years. The personnel following their usual treatment (control group) and those following the global prevention program in addition to their usual treatment (intervention group) are compared in terms of low back pain recurrence and the impairments measured at the beginning and the end of the study. The global prevention program is composed of a two-hour information session about low back pain and pain pathways, followed by five weekly 90-min exercise sessions with one physiotherapist per group of eight to ten personnel. A booklet for home use with patient-managed exercise instructions and information (The Back Book) is given to each participant at the end of the program.

An X-ray assessment of the entire spinal column of each participant (in both the control and intervention groups) is performed at the onset of the study in order to analyze sagittal spinopelvic balance as well as lombopelvic morphotype.

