### Randomization

Following the inclusion visit, the study group of the participants was decided by random allocation. The randomization was stratified and balanced by blocks between the participating occupational health services. The randomization lists were computed using SAS® statistical analysis software (Version 9.1, SAS Institute Inc., Cary, NC).

Each participant was informed by mail of his assignment to a study group following an entry checkup performed by a physiotherapist. In this letter, the study group was identified and, where appropriate, the timetable for the five global prevention program sessions was included. In order to ensure the objectivity of the evaluations, the occupational health physicians were not informed as to which study group each participant was assigned (single blind). At the time of enrollment, participants were also asked not to reveal their study group to the occupational health physician.

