##### Training program

The training program involves five weekly sessions of 90 min each. The sessions are led by a physiotherapist from the Centre Médico-Chirurgical et de Réadaptation des Massues – Croix Rouge Française, in a rotating manner in order to limit the therapist effect. The patients meet in a group of eight to ten persons.

Each rehabilitation session is composed of three parts: first, a warm-up (15 min) with rhythmic exercises and changes in rhythm (walking forward, backward, on tiptoe, on heels, and so on); second, a period for stretching and mobilizing the rachis (60 min) including relaxation of the lumbar rachis and stretching of the hamstrings, gluteals, quadriceps, psoas and adductors, as well as pelvic tilt awareness exercises; and finally, a third part involving respiratory and postural work (15 min).

The program was conceived in a spirit of continuity and progression from one session to the next. A patient is therefore not allowed to pursue the program in case of absence (except for session 3 or session 4, which are very similar to each other, so one of these sessions can be substituted for the other).

The aims of the training program are: 1) to improve the patient’s knowledge and management of his back through practical education and theoretical explanations; 2) to lessen motor inhibition and the fear of movement through the use of simple, repeated exercises, in the aim of leading the participants toward awareness of their avoidance behavior and encouraging them to resume physical activity; 3) to reinforce global postural control and proprioceptive control; and 4) to raise awareness of factors that can modulate pain.

The physiotherapist emphasizes the purpose of each exercise and also suggests personalized exercises. The aim is to explain techniques and assist participants in their practical acquisition, so that the participants can learn to know and maintain their back.

The training sessions are carried out on the workplace site of the participants in a room that is appropriate for floor exercises.

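### The physiotherapists who run the 18-month impairment tests fall outside the blinding rule and are likely to learn the arm, so the endurance and flexibility comparison can lean toward the program

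*Protocol article*

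**What the plan says.** The Methods/Design part of the abstract says that the two groups "are compared in terms of low back pain recurrence and the impairments measured at the beginning and the end of the study". The section Evaluation of deficiencies states who measures these and when: "Information relative to impairments is collected by the physiotherapist at the baseline and the 18-month follow-up visits". It lists ten items. Two are participant-reported (the pain questionnaire and the visual analog scale). Four are flexibility measures (items 3 to 6) and four are endurance tests (items 7 to 10).

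Under Follow-up visits, the 18-month visit is carried out "by a physiotherapist from the Centre Médico-Chirurgical et de Réadaptation des Massues – Croix Rouge Française (one appointment after 18 months"). Under Training program, the same centre provides the trainers: "The sessions are led by a physiotherapist from the Centre Médico-Chirurgical et de Réadaptation des Massues – Croix Rouge Française, in a rotating manner".

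The section Assessment of compliance with the global program adds a task to that visit: "compliance is evaluated by the physiotherapist during the 18-month follow-up visit using a five-class semi-quantitative ordinal scale". The thing rated is how well the home exercises are executed. Under Home-based program, "The exercises in this home-based program are taught during the supervised training program sessions", and the control group section gives that arm no such program.

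The masking rule is in Randomization: "the occupational health physicians were not informed as to which study group each participant was assigned (single blind"). The accompanying request that participants keep their group to themselves also names only the occupational health physician. The Discussion calls the trial open and answers the concern about bias by pointing to the objectivity of work absence.

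**The concern.** The protocol sets up masking so that evaluations are objective, then applies it to one group of evaluators only. The other group, the physiotherapists, carries out the hands-on tests. How long a participant holds an abdominal, lumbar extensor, gluteal or quadriceps position depends on effort, on the examiner's encouragement and on when the examiner stops the test. Flexibility readings depend on positioning.

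An examiner who belongs to the delivering centre and learns the arm could, without intending to, produce a difference in these measures where none exists. The expected direction is in favour of the program. What is at stake is the credibility of the only examiner-measured physical comparison between the arms.

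**Working it through.** The point disputes no figure in the protocol, so the main check sets the sections side by side.

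1. **Is a between-arm comparison planned?** Yes, according to the abstract. It speaks of the beginning and end of the study. The only impairment measurement after baseline is the 18-month visit, which Table 1 calls the final physiotherapy assessment, so that visit supplies the comparison.
2. **Who examines?** Physiotherapists of the centre that delivers the sessions (Follow-up visits; Training program). Trainers rotate, "in a rotating manner in order to limit the therapist effect", so an intervention participant may have met more than one of them.
3. **Is the examiner masked?** No. Both the masking and the non-disclosure request in Randomization stop at the occupational health physicians.
4. **Does the visit itself reveal the arm?** It is likely to. Rating the execution of exercises taught to one arm only identifies that arm once the rating is done, or once the examiner knows it is due.
5. **Is baseline equally exposed?** Not on the participant's side. Participants learn their assignment by mail after the entry checkup. Adjusting for baseline would therefore not remove a shift that arises at 18 months.
6. **Which items are exposed?** Ten items less two participant-reported items leaves eight.
7. **Does the stated defence reach them?** No. The objectivity argument in the Discussion concerns sick leave only.

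**Size.** The document gives nothing from which to estimate the bias. The following shows sensitivity under an assumption and is not an estimate. It uses the planned 310 per group. That figure is consistent with its stated inputs: 45% against 0.75 × 45% = 33.75%, two-sided 5%, 80% power gives 295 per group without continuity correction and 313 with it.

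Standard error of a standardized mean difference: √(2/310) = 0.080 SD. With no true effect and an assumed examiner shift of *b* SD, the chance of a significant result in favour of the program is Φ(*b*/SE − 1.96):

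| Assumed shift (SD) | Shift / SE | Chance, 310 per arm | Chance, 250 per arm |
|---|---|---|---|
| 0 | 0 | 2.5% | 2.5% |
| 0.05 | 0.6 | 9% | 8% |
| 0.10 | 1.2 | 24% | 20% |
| 0.20 | 2.5 | 70% | 61% |
| 0.30 | 3.7 | 96% | 92% |

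The 250 column allows for lower attendance, which is also an assumption. The table shows only that, at this sample size, a modest systematic shift would matter. It does not show that such a shift exists.

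**The case against.** The strongest case on the other side concerns weight.

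- **Rank of the measures.** Impairments appear under Other parameters, outside the primary outcome and the five secondary outcomes, and the analysis sections specify no test for them. The sick-leave outcomes are gathered by the masked physicians. This stands, and it limits the point to the impairment comparison that the abstract announces.
- **Knowledge of the arm.** A reader might infer that the examiner knows the arm before testing begins. The document does not say so. It does not say that the examiner trained that participant, nor in what order the tests and the rating are done, and a condensed article may leave visit order to the full protocol. The program lasts about two months, so the visit falls roughly 18 − 2 = 16 months after the last session, when recognition is less certain. Likely knowledge is supportable; certain knowledge is not.
- **Other explanatory measures.** A reader might also infer that these tests are the only between-arm evidence on how the program works. They are not. Self-reported disability, fear-avoidance and coping are collected at 18 months too, and reducing fear of movement is a stated aim of the training.
- **Acknowledgement.** The Discussion admits that the lack of double blinding could bias interpretation. That is a general admission. It does not mention the physiotherapists' tests, and its remedy does not cover them.
- **Timing.** Inclusion ran from October 2008 to July 2011, so 18-month visits began around spring 2010. Any change of procedure would miss visits already made.

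**Conclusion.** The point holds as a design weakness in a stated but unranked comparison. The 18-month examiner is unmasked, comes from the delivering centre and has a task at that visit that is likely to reveal the arm. Items 3 to 10 can therefore be biased toward the program. That the arm is learned is a strong inference from the sections read together; that the bias favours the program is the expected direction and has not been demonstrated. Its size is unknown, and the shifts tabulated above are assumptions.

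A reader might extend this to the trial's efficacy conclusion. The document does not support that: the primary outcome and the sick-leave-based secondary outcomes do not pass through the physiotherapist. The change is worth making because it is cheap and protects a comparison that the abstract announces.

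**What to change.** 1. Extend the non-disclosure request in Randomization to the 18-month physiotherapist, to hold until the impairment tests are closed.
2. Complete and close the impairment tests before the exercise-execution rating at that visit.
3. Where existing staffing allows, assign the visit to a physiotherapist who led none of that participant's sessions. The number of physiotherapists is not given and trainers rotate, so this cannot be promised for everyone.
4. Report the examiner-run impairment results as unblinded for any visit where these steps were not followed. This remains possible at any stage, including after all visits are done.

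Steps 1 and 2 need one added instruction and a fixed visit order, with no extra staff or visit. Step 3 costs some scheduling freedom. If steps 1 to 3 are adopted partway through the trial, measurement conditions will differ between earlier and later visits, and the report should say so.
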